### Workflow in Primary Health Care Clinics

#### Workflow in Clinics Using Paper-Based Systems

Pregnant women visit primary health care clinics for their first antenatal (booking) visit on specific workdays (clinics may work 1-4 days a week). The nurse or midwife in the clinics receives the pregnant women for the booking visit and documents a set of demographic data (eg, name, national identification number, address, phone number, and date of birth), and medical, surgical, and obstetric history. Afterward, the nurse or midwife measures and documents the woman’s height and weight, blood pressure, and fundal height and orders and fills out routine laboratory results appropriate for each antenatal visit. As part of the booking visit, the doctor examines women on the same workday or a few workdays later in some clinics. The nurse or midwife assists the doctor in medical and ultrasound examinations. For pregnant women identified with risk factors that warrant a referral, the nurse or midwife makes necessary arrangements for transfer to the referral health facility. There is a flexible appointment system for all subsequent antenatal visits. For uncomplicated pregnancies, the nurse or midwife documents blood pressure and fundal height, checks for fetal presentation, and orders laboratory investigations during the subsequent antenatal visits. Nurses and midwives typically do client care for pregnant and postpartum women as well as newborns in the first part of the workday. Following this, the nurse or midwife usually completes registers for antenatal care, referrals, ultrasounds, vaccines, and laboratory investigations. The nurse or midwife also compiles the data in the registers for public health reporting to the Palestinian Ministry of Health, typically concentrating this task in 1 or 2 workdays monthly. Event counts of number of pregnancies registered in the clinic, number of ultrasound examinations and laboratory tests that are performed, and number of pregnancies with risk conditions that are referred are some examples of the data that are part of standardized monthly reports submitted by care providers [25].

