#### Sampling

For sample size estimations, we assumed that clinics using paper-based systems spend an average of 10 min on health information management per client. We also assumed unequal and higher SD around the mean health information management time (in minutes) for clinics that use the eRegistry (SD=5) compared with clinics that use paper-based systems (SD=2) because of an expected variance in computer literacy and confidence of use. Sample size calculations were made using the Stata command “clustersampsi” to detect a 25% difference at a 90% power and 5% significance using an a priori intracluster correlation coefficient of .1 [28,29]. A total of 24 primary health care clinics were selected to be observed, 12 from each arm of the CRCT, with at least 8 observed antenatal consultations per clinic (Figure 1). Statisticians that are independent of the eRegTime study team performed a random sampling of the primary health care clinics for the observations, stratified on laboratory availability.

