### Data Analyses

The unit of measurement of the primary outcome is the time spent on health information management per client per care provider, where time will be analyzed in minutes. Statistical analyses will be performed using Stata version 15 or later (StataCorp LLC, 2017,  *Stata Statistical Software: Release 15*) or RStudio version 1.2.1335 or later. Descriptive statistics for the time variables will be summarized as means and SDs. We will report on the average time spent on antenatal consultation overall, and for booking visits and other antenatal visits separately, and the average time spent on each of the activity types including those that are not part of the primary outcome (including “client care,” “client-related care,” and “miscellaneous”; see Table 1).

We assume that the nurse or midwife spends, on average, an equal amount of time on after-consultation documentation work per client. The after-consultation time spent on client-related documentation and public health reporting will be averaged over the number of observed antenatal consultations and added to the time spent per consultation. Differences in the health information management time between the clinics with and without the eRegistry will be tested for significance using the linear mixed effects model to account for clustering [33,34]. In addition, as secondary analyses, we will test for differences in the health information management time separately for booking visits and other antenatal visits, and differences in time spent on other activity types in the 2 arms. Postpartum care consultations will be excluded from the analysis, as the focus of both eRegQual and eRegTime studies is on antenatal care quality and clinical processes.

Accompanying the results of the outcomes of the study, interobserver reliability assessments will be reported using kappa coefficients for the total number of clinical tasks and activity types recorded and intraclass correlation coefficients for the recorded mean times for the tasks and analysis categories (see Table 1) [35].

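### The primary mixed model, as stated, leaves visit type (booking or other) to secondary tests; adjusting for it would gain precision at no cost

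*Protocol article*

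**What the plan says.** Under Data Analyses, the protocol article states that the difference between clinics with and without the eRegistry "will be tested for significance using the linear mixed effects model to account for clustering". Clustering is the only feature of the model that it names. Visit type comes next, as a secondary matter: "we will test for differences in the health information management time separately for booking visits and other antenatal visits". The same section promises average consultation times by visit type, so each consultation must be identifiable as booking or other.

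The section also sets how work done after consultations is shared out: "We assume that the nurse or midwife spends, on average, an equal amount of time on after-consultation documentation work per client". That time is averaged over the observed antenatal consultations and added to each.

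The workflow section for paper clinics describes the two kinds of visit. At booking, the nurse or midwife "receives the pregnant women for the booking visit and documents a set of demographic data", then medical, surgical and obstetric history, then measurements and laboratory results. For an uncomplicated later visit it lists only blood pressure, fundal height, fetal presentation and laboratory orders.

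Three sections bear on the visit mix. Eligibility Criteria sets an average floor of one booking visit per workday. Sampling stratifies on laboratory availability only. Data Collection Methods takes all antenatal consultations of the observed day and adds days until a clinic reaches 8.

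**The concern.** Documentation is a major component of the primary outcome, and booking visits carry more of it. Visit type is therefore likely to be a strong predictor of the outcome. The mix is left to chance across about 96 consultations per arm (12 clinics of 8). It may also cluster by clinic, because booking visits are held on specific workdays and a clinic may be observed on only one day.

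A model without visit type leaves that variation in the error. The interval is then wider than it need be, and a chance difference in booking share moves the observed contrast. The planned by-type tests do not address this. They split the data, rest on few booking visits, and give no adjusted overall effect. They also give both visit types the same after-consultation constant, so they cannot show any difference between types in that work.

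**Working it through.** **Inputs from Sampling.** The article assumes that "clinics using paper-based systems spend an average of 10 min on health information management per client", with SD 2 min for paper and 5 min for the eRegistry. The calculation was made "to detect a 25% difference at a 90% power and 5% significance using an a priori intracluster correlation coefficient of .1". The target is therefore 2.5 min, with 12 clinics per arm and at least 8 consultations each. Two-sided testing is assumed.

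**The plan's own figure.**
- Individuals per arm: (1.960 + 1.282)² × (2² + 5²) / 2.5² = 48.8.
- Design effect: 1 + (8 − 1) × 0.1 = 1.7, which gives 82.9 per arm, or 10.4 clinics.
- With t quantiles on 2(k − 1) degrees of freedom the need is 11.4, so 12 clinics. The stated number reproduces.
- Power at 12 × 8 is 93.7% (normal), 91.5% (noncentral t, 22 df) or 90.1% (Welch df).
- Variance of the contrast: 29 × 1.7 / 96 = 0.514, so SE = 0.717 min.

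**Assumed inputs, not in the documents.** Booking share p = 25%; booking visit longer by D = 2 to 4 min; intracluster correlation of visit type ρ = 0 to 0.1.

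D has an upper limit. Visit type contributes D²p(1 − p) to the within-arm variance. The paper-arm total is 2² = 4, so at p = 25% D cannot exceed √(4 / 0.1875) = 4.6 min without contradicting the planning SD.

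**Chance shift.** The SD of the arm difference in booking share is √[2p(1 − p)(1 + 7ρ)/96]. This is 6.25 percentage points at ρ = 0 and 8.1 at ρ = 0.1. A difference of 10 points or more then arises in about 11% to 22% of samples. Multiplying by D gives the shift in the contrast. The last two columns give its share of 0.514 and the SE once that share is removed, 0.717 × √(1 − share), taking the planning SDs to include visit mix.

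| D (min) | ρ | SD of shift (min) | 95% range (min) | Share of variance | Adjusted SE (min) |
|---|---|---|---|---|---|
| 2 | 0 | 0.12 | ±0.24 | 3.0% | 0.706 |
| 2 | 0.1 | 0.16 | ±0.32 | 5.2% | 0.698 |
| 4 | 0 | 0.25 | ±0.49 | 12.2% | 0.672 |
| 4 | 0.1 | 0.33 | ±0.64 | 20.7% | 0.638 |

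**Simulation.** There were 4,000 trials per scenario. Clinic means were compared by a Welch test as a stand-in for the mixed model, with the planning SDs taken to include visit mix and p = 25%.

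| D (min) | True difference (min) | Unadjusted: mean, SE, rejection rate | Adjusted: mean, SE, rejection rate |
|---|---|---|---|
| 2 | 0 | −0.006, 0.715, 4.6% | −0.006, 0.696, 4.5% |
| 2 | −2.5 | −2.512, 0.723, 89.4% | −2.509, 0.705, 91.0% |
| 4 | 0 | −0.008, 0.723, 5.5% | −0.003, 0.649, 5.5% |
| 4 | −2.5 | −2.520, 0.716, 90.2% | −2.520, 0.641, 94.6% |

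The unadjusted estimate is centred on the truth and its type I error is about 5%. The gain from adjustment is in precision.

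**If the planning SDs exclude visit mix.** The extra variance is then on top. Unadjusted power (noncentral t) falls from 91.5% to between 90.7% (D = 2, ρ = 0) and 85.9% (D = 4, ρ = 0.1).

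**Booking-only test.** A 25% share of 8 is two booking visits per clinic. With the planning SDs and correlation 0.1, SE = √(29 × 1.1 / 24) = 1.15 min, and power for 2.5 min is Φ(2.5/1.15 − 1.96), about 58%. No SD specific to booking visits is given, so this is only indicative.

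**The case against.** A reader might infer that leaving out visit type biases the primary comparison. The documents do not support that. Arms were randomised and clinics sampled at random, so a chance difference in mix is sampling error, and the model's standard error already reflects it. The article shows no systematic cause of a different mix between arms.

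A reader might also infer that the trial is underpowered as a result. The planning SDs describe time per client and are not limited to one visit type, so they may already contain the visit mix. In that case the 12 × 8 design keeps about 90% power, and adjustment is a bonus rather than a repair.

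Larger effects can be produced by supposing that a booking visit takes 5 or 10 min longer. At a 25% share, visit type alone would then contribute 4.7 or 18.8 min², more than the planned paper-arm total of 4, so those cases contradict the plan they are meant to test. Likewise, power of about 36% for the booking-only test needs one booking visit per clinic, which does not fit a 25% share of 8. The by-type tests were in any case never claimed to be powered.

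It is also fair to say that the plan does not ignore visit type, and that a condensed article may leave covariates to an analysis plan that is not shown. That limits the strength of the point. It does not remove it, because the article does say where visit type enters, and that is only in secondary tests.

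Finally, whether a booking visit needs more after-consultation register work is conjecture. Several of the registers listed (referrals, ultrasound, vaccines, laboratory) are not specific to booking.

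**Conclusion.** The point holds as a matter of precision. The primary model as stated omits a recorded and probably strong predictor that the design does not balance. The estimate remains unbiased in expectation and the test keeps its level.

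With a 25% booking share, an extra 2 to 4 min and a visit-type correlation up to 0.1, adjustment takes the SE from about 0.72 to between 0.70 and 0.64 min and power from about 90% to between 91% and 95%. The 95% range of the chance shift is ±0.24 to ±0.64 min, against a target of 2.5 min. At 2 min the gain is slight; near 4 min it is worth having. Share, time difference and correlation are all assumptions, so the true size cannot be fixed from the documents. This is an inexpensive improvement, not the correction of an invalid analysis.

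**What to change.** 1. Prespecify visit type (booking or other) as a fixed effect in the primary linear mixed model, and keep the single overall arm effect as the primary estimate. An arm-by-visit-type interaction should not go into this model, because the arm coefficient would then refer to one visit type and no overall effect would be defined.
2. Replace the separate by-type tests with one secondary model that includes the interaction, and report the arm effect with an interval for each visit type. This does not add booking visits, so those intervals will still be wide for bookings.
3. Repeat that secondary model on in-consultation time only, as a sensitivity analysis, because the equal split adds the same constant to both visit types. It cannot replace the main by-type analysis, since after-consultation documentation and reporting belong to the outcome under Outcome Measures.

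The cost is one covariate that the article already commits to reporting by, with no extra data. The Results section places the analysis after data collection but still ahead, so the change should be recorded before outcomes are compared by arm.

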### Ethics Approval and Consent to Participate

The eRegTime study was approved by the Palestinian Health Research Council (PHRC/HC/208/17) and the Regional Committee for Medical and Health Research Ethics in Norway (2017/400). Permissions to conduct observations in the clinics have been obtained from the Palestinian Ministry of Health. Care providers and supervisors of the primary health care clinics will be informed of the data collection for this study. Considering the local sensitivity and hesitance related to signing documents in our study context, pregnant women will be asked for oral consent to allow the observers to be present in the rooms during consultations, and the ethics committees were notified of this. No data will be recorded on personal or individual characteristics of pregnant women, care providers, or primary health care clinics. Only completely anonymous data will be available to the researchers for analysis.

## Results

Ethical approvals for conduct of the study were obtained in April 2017. The data collection tool was designed, tested, and adjusted over 2017 and 2018, followed by which the sample was selected for the main study. Clinics included in the sample were informed about the study before start of observations, and the data collection for the eRegTime study was completed between August and December 2018. Data will be analyzed for outcomes in July and August 2019; the results are expected to be published in the second half of 2019.

## Discussion

The eRegTime study is one of the few studies that assesses the impact of an eHealth intervention on clinical workflow and time-efficiency in a middle-income context, where the impact of using digital tools routinely during clinical care is probably much bigger given the manpower and resource constraints than high-income settings.

Most studies that have assessed the time-efficiency using the time-motion design find no statistical differences in the workload of care providers following the introduction of eHealth tools [15,30,31,36]. Factors that may potentially affect the time-efficiency of care providers while using eHealth tools are duration of use of eHealth tools, computer literacy, multitasking, and interruptions [37-41]. In some settings, a period of 18 to 24 months between the implementation of the eHealth tools and the observations was considered sufficient for the stabilization of clinical work routines [15,42]. Primary health care clinics observed in the eRegTime study will be using the eRegistry for a median time of 20 months at the time of the observations. According to a questionnaire survey conducted in the intervention clusters of the eRegQual CRCT, a quarter of the nurses and the midwives had never used a computer before starting to use the eRegistry. Formative research and workflow mapping exercises showed that health care service delivery in the setting of this study was characterized by fragmented workflow and the time taken to perform the different tasks was relatively short [27]. The time-motion design is particularly suitable for data collection in such settings [30,31]. Although interruptions to the workflow and multitasking might be overlooked because of the fact that the data collection tool requires the observer to select only 1 activity at the time, the primary objective of the eRegQual study is to assess quantitative differences in time spent between clinics with and without the eRegistry; data collection methods were designed to be identical in the 2 arms.

Other methods such as work sampling and self-reported questionnaires were considered during the planning phase of this study. However, with work sampling, in which activities are recorded only at certain time intervals, there is a risk of missing certain activities. In addition, this method requires an enormously large sample size, which was not feasible in our setting [43]. The use of self-reported questionnaires poses risks of inaccurate reporting and recall bias as well as being a considerable interference to the care provider’s workflow [44]. The time-motion design was therefore considered the most suitable for this study.

We acknowledge that it may not be possible to completely eliminate the risk of care providers behaving differently because they know they are being observed [45]. We will attempt to minimize this effect by training the observers to avoid interfering with clinical work [45]. Another potential source of bias is diverging subjective interpretations of the tasks during data collection by the observers, and this will be minimized by hands-on training sessions, practice sessions with simulation videos, and “test” observations before the start of the study observations.

## Appendix

Multimedia Appendix 1 Suggested Time and Motion Procedures (STAMP) checklist.

Multimedia Appendix 2 SPIRIT protocol checklist.

Multimedia Appendix 3 Training manual.

## Abbreviations

CRCT: cluster randomized controlled trial
DHIS2: District Health Information System 2
eHealth: electronic health
eRegistry: electronic registry
LMIC: low- and middle-income country
